#### 2.2.2. Metabolic Biomarkers of Histamine in Urine

The urinary profile of histamine metabolites is assessed using both targeted and untargeted approaches to evaluate the potential impact of the dietary intervention. Spot urine samples (first morning urine) are collected and kept under refrigeration until delivery to the laboratory, where they are immediately aliquoted and stored at –80 °C until analysis. Prior to chromatographic analysis, urine samples are thawed, centrifuged, and diluted 50 µL 1:1 with Milli-Q water. Histamine and its three main metabolites (1-methylhistamine, imidazole acetic acid, and methylimidazole acetic acid) are identified and quantified by LC-ESI-MS/MS, using their respective deuterates as internal standards. Untargeted analysis is carried out by HPLC-TOF-MS according to the method described by Llorach et al. (2013) [48]. Data are extracted and aligned using commercial software, such as MarkerView 1.3 (Sciex, Framingham, MA, USA), or non-commercial software, such as MAIT [49]. Data analysis is conducted using unsupervised multiparametric tools, such as principal component analysis and hierarchical cluster analysis, as well as supervised multiparametric algorithms, such as PLS-DA with orthogonal signal correction [48,50].

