## 2. Materials and Methods

### 2.1. Study Design

This prospective, unicentric, double-blind, randomized, and placebo-controlled trial is being performed by a multidisciplinary team of researchers from the Food Bioactive Amines and Polyamines research group at the Food and Nutrition Campus, University of Barcelona, and the Cardiovascular Risk, Nutrition, and Aging research group at the August Pi i Sunyer Biomedical Research Institute (IDIBAPS) of the Hospital Clínic de Barcelona. The study commenced in June 2022 and is expected to conclude in May 2025.

The study design is outlined in Figure 2. In this protocol, participants are randomized into eight study groups (50 individuals/group), based on combinations of diet (low-histamine or control diet) and supplementation (placebo, porcine DAO, and two different doses of plant-based DAO). The intervention period lasts three months.

The sample size is calculated considering the average number of symptoms reported by histamine-intolerant patients and the standard deviation (11.1 symptoms/patient ± 4.8) [6]. To detect a variation in at least two symptoms per patient, assuming an alpha risk of 0.05 and a beta risk of 0.02 in a bilateral contrast, a minimum of 42 participants per group is required. To accommodate a 10% drop-out rate, 50 participants will be recruited for each group. Therefore, as the study includes eight intervention groups, the total number of participants is 400.

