#### 2.1.2. Baseline Visit and Randomization of Participants

During the baseline visit, a trained nurse administers a questionnaire to record demographic data and a complete medical history, including alcohol consumption and smoking habits (Supplementary Figure S1). Additionally, participants complete various validated questionnaires specific to each symptom of histamine intolerance (described below). Comprehensive information on dietary habits is collected through a validated 151-item semi-quantitative food frequency questionnaire (FFQ), a seven-day dietary recall (for the seven days prior to the visit), and either a 14-item Mediterranean diet adherence screener (for control diet) or a low-histamine diet screener, administered by trained dieticians in face-to-face interviews [32].

The same trained personnel then collect anthropometric measurements, determine blood pressure (BP), and extract a blood sample to analyze biochemical parameters. Height is measured to the nearest 0.1 cm using a wall-mounted stadiometer, with subjects standing, wearing socks, and maintaining their heads in the horizontal plane. Body weight is recorded to the nearest 0.1 kg, with participants in light clothing, without shoes or accessories, and using a high-quality calibrated scale. Body mass index is calculated by dividing weight (kg) by the square of height (m^2^). Waist circumference is measured midway between the lowest rib and the iliac crest using an anthropometric tape, and hip circumference is measured at the maximum point below the waist, without compressing the skin [33]. BP is taken in triplicate after at least five minutes of rest using a validated semiautomatic oscillometer (Omron HEM-705CP, Hoofddorp, The Netherlands). The clinical analyses include a basic biochemical profile (i.e., glycemia, lipid profile, creatinine, urea, hepatic function parameters, and total proteins and albumin) and serum histamine and tryptase levels. All these analyses are performed in the CORE laboratory of Hospital Clinic following in-house routine procedures and meet all required quality criteria, receiving ISO 9001:2015 certification [34] and ISO 15189:2022 accreditation [35] for some tests.

At this point, participants provide urine and stool baseline samples for the study of metabolomic biomarkers of histamine and intestinal microbiota, respectively (described below). Samples are processed after collection and stored in −80 °C freezers.

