#### 2.1.4. Follow-Up and Final Visits

The evolution of symptoms, urinary profile of histamine metabolites, and intestinal microbiota composition, as well as anthropometric measurements and blood biochemical parameters, including the basic biochemical profile and histamine and tryptase, are assessed after the first and second month (follow-up visits) and the third month (final visit) of the dietary intervention (Figure 2). Serum DAO activity will also be measured during the final visit.

Dietary compliance is assessed using seven-day food records and adherence tests for the low-histamine diet or Mediterranean diet [32]. Unlike the validated Mediterranean diet adherence screener, there is no standard test for assessing compliance with a low-histamine diet. The present research will validate the low-histamine diet adherence test prepared *ad hoc* for this study.

Throughout the intervention period, participants receive a phone call every two weeks to assess correct adherence to the study protocol and to monitor for any unexpected secondary effects.

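### For a urinary metabolome sampled four times per patient, section 2.2.2 names only methods with no within-person or baseline component; the patient should be made the unit of analysis

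*Protocol article*

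**What the plan says.** Protocol article, section 2.1.2: at the baseline visit "participants provide urine and stool baseline samples for the study of metabolomic biomarkers of histamine and intestinal microbiota". Section 2.1.4 adds three later time points: "The evolution of symptoms, urinary profile of histamine metabolites, and intestinal microbiota composition", among other measures, "are assessed after the first and second month (follow-up visits) and the third month (final visit) of the dietary intervention". That makes four urine samples per patient.

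Section 2.2.2 gives the aim. The urinary profile "is assessed using both targeted and untargeted approaches to evaluate the potential impact of the dietary intervention". For analysis it names "unsupervised multiparametric tools, such as principal component analysis and hierarchical cluster analysis" and "supervised multiparametric algorithms, such as PLS-DA with orthogonal signal correction". Both lists are examples, and the section refers to cited methods papers. It mentions no paired, multilevel or change-from-baseline step.

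Section 2.2.1, by contrast, does provide baseline adjustment (analysis of covariance), but for the symptom questionnaires. Section 2.1 fixes the design: "participants are randomized into eight study groups (50 individuals/group".

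**The concern.** Patients are randomised, but urine samples are measured, and each patient supplies several. A person's urinary profile is partly stable over time. The methods named see only rows of a data matrix. If the rows are samples from several visits, they cannot tell four samples from one patient from four samples from four patients.

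Suppose the visits are stacked and cross-validation folds are drawn over samples. Then a patient in the held-out fold usually also has samples in the training folds. The classifier can recognise the person, and every sample from that person carries the same arm label. Accuracy then exceeds chance even if the intervention does nothing. Shuffling labels over samples would not expose this, because it breaks the link between person and label that causes the problem.

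At stake are the apparent separation between arms in the untargeted metabolome and the list of metabolites selected from it. For a before–after comparison the direction differs: ignoring the pairing mainly hides a real change.

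**Working it through.** The article states no figure for this analysis, so there is none to reproduce. The check has three parts.

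**1. Samples and information.** Inputs: 8 groups × 50 = 400 patients (section 2.1); 1 baseline + 3 later samples = 4 per patient (sections 2.1.2 and 2.1.4). Without drop-out, 400 × 4 = 1,600 samples. With within-patient correlation r, the design effect is 1 + (4 − 1)r. The article gives no r, so 0.3, 0.5 and 0.7 are assumed:

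| r | Design effect | 1,600 samples are worth |
|---|---|---|
| 0.3 | 1.9 | 842 |
| 0.5 | 2.5 | 640 |
| 0.7 | 3.1 | 516 |

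**2. Null simulation.** There is no arm effect, so true accuracy is 0.50. Assumptions: 300 independent Gaussian features, PLS-DA with 3 components, 7-fold cross-validation, four visits, 15 runs per setting. The 200 v 200 contrast is diet (4 × 50 per side); 50 v 50 is any two of the eight groups.

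| Contrast | r | Pooled, folds by sample | Pooled, folds by patient | Final visit only | Change from baseline |
|---|---|---|---|---|---|
| 200 v 200 | 0.3 | 0.604 | 0.494 | 0.503 | 0.509 |
| 200 v 200 | 0.5 | 0.663 | 0.493 | 0.479 | 0.487 |
| 200 v 200 | 0.7 | 0.718 | 0.489 | 0.489 | 0.492 |
| 50 v 50 | 0.3 | 0.705 | 0.487 | 0.472 | 0.498 |
| 50 v 50 | 0.5 | 0.826 | 0.489 | 0.501 | 0.479 |
| 50 v 50 | 0.7 | 0.938 | 0.497 | 0.493 | 0.503 |

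Pooling only the three on-treatment visits gives much the same with 2 components and 40 runs: 0.59, 0.64 and 0.70 for 200 v 200, and 0.68, 0.79 and 0.88 for 50 v 50. Folds by patient return 0.49–0.51. A further run gave 0.59–0.70 and 0.67–0.89. Across all runs, the false accuracy is 0.59–0.72 for 200 v 200 and 0.67–0.94 for 50 v 50.

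The orthogonal signal correction step was not simulated separately. It removes variation unrelated to the class label, but it does not model the person or keep one patient's samples in one fold. In its O-PLS form, with the same total number of components, it gives the same predictions as PLS.

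**3. What a single-visit analysis gives up.** Take one feature with variance 1 at each visit, equal correlation r between visits and an effect constant over months 1 to 3. The per-patient variance behind the arm contrast is:

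| Analysis | Formula | r = 0.3 | r = 0.5 | r = 0.7 |
|---|---|---|---|---|
| Final visit only | 1 | 1.00 | 1.00 | 1.00 |
| Final minus baseline | 2(1 − r) | 1.40 | 1.00 | 0.60 |
| Final, adjusted for baseline | 1 − r² | 0.91 | 0.75 | 0.51 |
| Mean of months 1–3, adjusted for baseline | (1 + 2r)/3 − r² | 0.44 | 0.42 | 0.31 |

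Adjusting for baseline is never worse than the final visit alone. Plain subtraction is worse when r is below 0.5. A simulation with a true effect pointed the same way: detection rose from 61–68% with the final visit only to 73–85% with the on-treatment profile adjusted for baseline. Those percentages depend on the effect put in, so only the direction carries over.

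**The case against.** A reader might infer that the plan treats every sample as a different person. The documents do not support that. Section 2.2.2 does not say what a row is, that visits are pooled, or how models are validated. The false signal needs both pooling and folds drawn over samples. The named method is sound on one visit, on change from baseline, or on pooled data with folds by patient, as the simulation shows. This objection stands in full, and the accuracy figures are therefore conditional.

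A reader might also infer that the diagnostic-biomarker claim in the Discussion rests on this artefact. It does not. That passage concerns telling histamine-intolerant people from others, not one arm from another.

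Nor does the simulation show that principal component maps or cluster trees would produce a false diet claim. It covered PLS-DA only, and the maps are descriptive.

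Finally, row definition and fold assignment are details that an article may leave to the full protocol or analysis plan, and the methods are introduced as examples. Their absence is no fault in itself. What remains is narrower: the article does choose a method family for a stated comparative aim, and every example lacks the structure that its own four-visit design calls for, while the questionnaires are adjusted for baseline.

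**Conclusion.** The point holds as a recommended improvement to the named method, not as a demonstrated error. The methods in section 2.2.2 leave two routes open, each with a cost:

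- **Pooled visits with folds by sample:** a null effect can look like 0.59–0.72 accuracy (200 v 200) or 0.67–0.94 (50 v 50).
- **A single visit:** the result is valid, but at r = 0.5 the variance is 1.00, against 0.75 with baseline adjustment and 0.42 with all on-treatment visits as well.

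These sizes rest on assumed within-patient correlation, feature count, component number and independent features, and on the untargeted profile being measured at all four visits, which is the natural reading of sections 2.1.4 and 2.2.2. The urinary profile is a secondary outcome, so the main symptom comparison is untouched.

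**What to change.** State in section 2.2.2, or in the analysis plan it relies on, that the patient is the unit in the untargeted analysis:

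- Use one baseline-adjusted row per patient, for example the month 1–3 profile adjusted feature by feature for the baseline value. Alternatively, use multilevel PLS-DA or ANOVA-simultaneous component analysis with diet, supplement and visit as factors. Arm is constant within a patient, so in a multilevel model its effect appears as a difference between arms in change over visits.
- Assign cross-validation folds and permutations by patient, and refit the orthogonal signal correction within each training fold, since it uses the class label.
- Confirm selected metabolites with a mixed model containing baseline value, visit, diet, supplement and their interactions, with a random patient effect and false-discovery-rate control.

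The minimum that removes the false signal is one row per patient or folds by patient; the rest recovers precision. The cost is wording and modest programming, with no new samples. The reported discrimination may be lower than from a pooled model.

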#### 2.2.3. Intestinal Microbiota Composition

To study the profile and composition of the intestinal microbiota, bacterial DNA is isolated from stool samples using the QIAamp Powerfecal pro DNA kit (Qiagen GmbH, Hilden, Germany) according to the manufacturer’s instructions, and the DNA concentrations are determined by NanoDrop 2000 (Thermo Fisher Scientific, Wilmington, DE, USA). Subsequently, the V3–V4 region of bacterial 16S rRNA is sequenced on the Illumina MiSeq platform. Bioinformatic analysis for bacterial composition will be performed using the EzBioCloud Database (ChunLab, Inc., Seoul, Republic of Korea). Differences among study groups will be analyzed using the Kruskal–Wallis test. Alpha diversity will be described using the Shannon–Weaver Index and Simpson’s Index and beta diversity using Bray–Curtis and UniFrac methods [51].

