### 2.2. Study Outcomes

#### 2.2.1. Symptoms of Histamine Intolerance

Symptoms related to histamine intolerance, listed in Figure 1, are evaluated through specific validated questionnaires as follows: (a) gastrointestinal manifestations are assessed by the Gastrointestinal Quality of Life Index (GIQLI) and Bristol Stool Scale [38,39]; (b) headaches by the Migraine Disability Assessment Scale (MIDAS) and Headache Impact Test (HIT-6) [40,41]; (c) respiratory symptoms by the Rhinoconjunctivitis Quality of Life Questionnaire (RQLQ) and Nasosinusual Symptoms Questionnaire (SNOT-22); and (d) dermatological manifestations by SCORing Atopic Dermatitis (SCORAD), the Itch Severity Scale (ISS), Quality of Life Index for Atopic Dermatitis (QoLIAD), and Dermatology Life Quality Index (DLQI) [42,43,44,45,46]. Additionally, the general quality of life of patients is assessed using the SF-36 Health Questionnaire [47].

Data obtained from these questionnaires will be used to evaluate the effectiveness of the dietary treatment in the improvement or remission of patient symptomatology. Differences among the study groups will be determined using covariance analysis with baseline parameters as covariates. A multivariate analysis adjusted for age, sex, and clinical parameters with significant baseline differences among groups will also be applied. These differences will be expressed as means (95% confidence intervals).

All collected data regarding symptomatology will also be used to assess potential correlations with other study outcomes, such the composition of intestinal microbiota, the urinary profile of histamine metabolites, serum DAO activity, plasma histamine levels, and DAO-encoding gene variants.

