## 3. Discussion

The study described here is the first prospective, unicentric, double-blind, randomized, and placebo-controlled trial designed to evaluate the efficacy of combining a low-histamine diet with DAO supplementation in alleviating symptoms of histamine intolerance. Previous intervention studies have reported positive outcomes for either the low-histamine diet or DAO supplementation, although most of them have certain limitations regarding the number of patients, follow-up period, and control group [11,12,13,14,15,16,17,18,19,20,21,22,23,24,25,26,27,28,29,30,31]. In this sense, the broad majority of these studies (18 out of 21) considered small patient cohorts (fewer than 56 participants), 61% of which did not even exceed 30 patients. Although the studies conducted by Sienbenhaar et al. (2016) and Cucca et al. (2022) included larger sample sizes (157 and 146 patients, respectively), both trials entailed a significant drawback, due to the absence of a control group in their design [20,24]. In fact, the lack of a control group (i.e., not following a low-histamine diet or receiving placebo supplementation) is a recurring limitation in many of these studies (16 out of 21). Only the work performed by Izquierdo-Casas et al. (2019) included a cohort of 100 patients diagnosed with headache and DAO deficiency, with 50% receiving porcine DAO supplementation and the other half receiving a placebo [30]. Regarding the duration of the intervention, most of the studies, with the exception of three [13,18,22], were limited to a maximum of 4 weeks. For example, Mušič et al. (2013) considered a longer dietary intervention period of up to 12 months, during which patients with DAO deficiency followed a low-histamine diet. However, only 20 patients were monitored, and there was a lack of a control group [18]. The current study aims to address all these limitations by involving a total of 400 patients, including a placebo-controlled group and an intervention period of 3 months. The study design, with distinct intervention groups following a low-histamine diet and/or receiving DAO supplementation, will allow for the assessment of the impact of each treatment separately, as well as potential synergistic effects. Additionally, this clinical trial is pioneering in its evaluation of DAO sourced from plants as a dietary supplement for managing histamine intolerance.

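### The eight-group Kruskal–Wallis test for microbiota names neither the baseline stool value nor the diet and supplement factors; a baseline-adjusted factorial model fits the aims better

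*Protocol article*

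**What the plan says.** Section 2.1 of the protocol article sets out the design: "participants are randomized into eight study groups (50 individuals/group), based on combinations of diet (low-histamine or control diet) and supplementation". That is a 2 (diet) × 4 (supplement) factorial.

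Stool is available before treatment. Section 2.1.2 states that "participants provide urine and stool baseline samples for the study of metabolomic biomarkers of histamine and intestinal microbiota, respectively". Section 2.1.4 lists microbiota composition among the measures that "are assessed after the first and second month (follow-up visits) and the third month (final visit) of the dietary intervention".

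For the microbiota analysis, section 2.2.3 says: "Differences among study groups will be analyzed using the Kruskal–Wallis test". It then lists two alpha-diversity indices and two beta-diversity methods. It names no covariate and no factor.

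Symptoms are treated differently. Section 2.2.1 says: "Differences among the study groups will be determined using covariance analysis with baseline parameters as covariates".

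The Discussion says that the design "will allow for the assessment of the impact of each treatment separately, as well as potential synergistic effects", and the Abstract makes the same claim for the comparison of the groups. The Discussion also allows, as an option, secondary analyses that combine intervention groups. It does not tie this to microbiota and names no contrast.

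**The concern.** The stated test does not match the question. A Kruskal–Wallis test over eight groups asks whether any group differs from any other, on 7 degrees of freedom. If it is significant, diet, a supplement or their combination could be the cause, and the test does not say which. The trial sets out to tell these apart.

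The test as stated also leaves information unused. Each participant's baseline microbiota is measured, and the same article adjusts for baseline when it analyses symptoms. A diet effect shared by four groups against four is a single contrast, but the omnibus test spreads it over seven degrees of freedom. What is at stake is the chance of detecting, and correctly attributing, an effect of diet or supplement on microbiota.

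**Working it through.** **Inputs from the article.** Eight groups of 50 and a 10% drop-out rate (section 2.1) give 50 × 0.9 = 45 completers per group, so N = 8 × 45 = 360.

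**Assumptions.** The article gives no effect size, SD, baseline correlation or power for microbiota, so there is no figure of its own to reproduce. I take a shift δ of 0.2, 0.3 or 0.4 SD, a correlation r between baseline and follow-up of 0.3, 0.5 or 0.7, and a two-sided 5% level.

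**Formulas for a diet-only shift.** The noncentrality for normal data is λ = Nδ²/4.
- Kruskal–Wallis, eight groups, follow-up values: noncentral chi-square, 7 df, noncentrality λ × 3/π.
- Kruskal–Wallis, two pooled diet arms: the same noncentrality on 1 df.
- Kruskal–Wallis, eight groups, change from baseline: noncentrality λ × (3/π) / [2(1 − r)], 7 df.
- Baseline-adjusted diet contrast in the factorial model: noncentral F, noncentrality λ / (1 − r²), with 1 and 360 − 9 = 351 df.

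**Numbers at 0.3 SD.** λ = 360 × 0.09 / 4 = 8.1, and 8.1 × 3/π = 7.73. The adjusted noncentralities are 8.1/0.91 = 8.90, 8.1/0.75 = 10.8 and 8.1/0.51 = 15.88.

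| Diet shift | Kruskal–Wallis, 8 groups | Kruskal–Wallis, pooled diet arms | Adjusted diet contrast, r = 0.3 / 0.5 / 0.7 |
|---|---|---|---|
| 0.2 SD | 0.22 | 0.46 | 0.51 / 0.59 / 0.75 |
| 0.3 SD | 0.49 | 0.79 | 0.85 / 0.91 / 0.98 |
| 0.4 SD | 0.78 | 0.96 | 0.98 / 0.99 / 1.00 |

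At 0.3 SD the step from 0.49 to 0.79 comes from using the diet factor. The further step to 0.85–0.98 comes almost entirely from baseline adjustment.

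**Change scores.** Running the eight-group test on change from baseline at 0.3 SD gives 0.35 / 0.49 / 0.75 at r = 0.3 / 0.5 / 0.7. This loses power below r = 0.5, breaks even there and gains above it. It stays below the adjusted contrast throughout.

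**Simulation check.** With 1,500 runs per setting, 45 per group, a 0.3 SD shift, and normal and lognormal data, the results were:
- eight-group Kruskal–Wallis 0.46–0.48;
- pooled diet arms 0.79–0.80;
- rank-based adjusted diet contrast about 0.82 / 0.89 / 0.96 at r = 0.3 / 0.5 / 0.7;
- type I error 0.04–0.06 for all of them.

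**Supplement effect.** If all three active supplements differ from placebo by 0.3 SD, λ = 360 × 0.09 × (3/4)(1/4) = 6.075. Eight-group Kruskal–Wallis has 0.37. The adjusted 3-df supplement test has 0.56 / 0.65 / 0.83.

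**A synergy pattern.** Suppose only one diet-plus-supplement cell shifts, by 0.6 SD. The total noncentrality is 45 × 0.36 × 7/8 = 14.175. It splits into diet 360 × 0.15²/4 = 2.025, supplement 360 × 0.3² × (1/4)(3/4) = 6.075, and interaction 14.175 − 2.025 − 6.075 = 6.075.
- Eight-group Kruskal–Wallis: 0.77.
- Adjusted diet main effect: 0.32 / 0.37 / 0.51.
- Adjusted supplement main effect, and likewise the adjusted interaction (each 3 df): 0.56 / 0.65 / 0.83.
- Adjusted joint 7-df test of all terms: 0.83 / 0.90 / 0.98.

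In this pattern the omnibus test beats the adjusted diet contrast at every r, and beats the 3-df tests unless r is high. The joint test from the full adjusted model beats it throughout.

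**The case against.** Kruskal–Wallis is a valid, familiar test for skewed abundance data and holds its type I error. Microbiota is an additional outcome in a condensed article, and details such as the visit, the transformation and the handling of many taxa may stand in a fuller plan. All of this stands, and it limits the weight of the point. It does not remove it, because the article does not leave the method open: it names one, and that method has no term for the factors that the trial wants to separate.

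The optional pooling of groups in the Discussion would recover much of the diet power (about 0.79 at 0.3 SD). That is a fair mitigation. But it is optional, general and secondary, and it brings no baseline adjustment.

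A reader might draw stronger conclusions that the article does not support:
- **That the test cannot use the baseline sample.** It could be run on change from baseline. Section 2.2.3 does not say whether values or changes are compared. The supportable statement is that no use of baseline is named.
- **That about 5 in 100 taxa will be false signals.** This presumes uncorrected testing of each taxon at 0.05. The article says nothing of the kind; its only 0.05 belongs to the sample-size calculation for symptoms.
- **That much of the available power is lost in general.** The loss depends on the effect pattern. In the one-cell synergy pattern the omnibus test has more power than an adjusted diet main effect. For that reason a remedy with main effects only would also fall short of the synergy aim.

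**Conclusion.** The point holds in a limited form. The stated microbiota test is valid but does not fit the factorial aims. It names no baseline adjustment and no diet, supplement or interaction term, so a significant result cannot by itself be attributed to a factor.

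It is also less efficient for main effects. For a diet-only shift of 0.2 / 0.3 / 0.4 SD its power is about 0.22 / 0.49 / 0.78, against 0.51–0.75, 0.85–0.98 and 0.98–1.00 for the adjusted diet contrast. These figures rest on 45 completers per group, a comparison of follow-up values, and assumed shifts and baseline correlations that the article does not give. The gap narrows for large effects. The change is worth making because it costs little.

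**What to change.** In section 2.2.3, replace the Kruskal–Wallis test for abundance and alpha diversity with a baseline-adjusted model, on ranks or on transformed values. Its terms should be diet, supplement, diet × supplement and the participant's baseline value. Code the factors so that the diet effect is averaged over supplements and the supplement effect over diets, and report the interaction as the test of synergy. For the Bray–Curtis and UniFrac distances, use a permutation test with the same factors.

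The cost is somewhat more analysis work, and the choice of ranks or transformation must be fixed before the data are seen. No new samples, visits or participants are needed.
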